## Abstract

**Background:**

Substantial investment has gone into research on the efficacy and effectiveness of pharmaceutical and nonpharmacologic interventions for chronic pain. However, synthesizing this extensive literature is challenging because of differences in the outcome measures used in studies of similar or competing interventions. The absence of a common metric makes it difficult to replicate findings, pool data from multiple studies, resolve conflicting conclusions, or reach consensus when interpreting findings.

**Methods:**

This study has a seven-member Advisory Council of chronic pain experts. Preliminary analyses will be performed on data from several large existing datasets; intermediate analyses will be performed using primary data collected from Amazon’s Mechanical Turk (MTurk); and cross-validation will use primary data collected from a nationally-representative, probability-based panel. Target sample size for both primary datasets is 1500. The three study aims are as follows:
Aim 1 will develop and evaluate links between the 29-item Patient-Reported Outcomes Measurement Information System (PROMIS®-29) and legacy measures used for chronic pain such as the Roland-Morris Disability Questionnaire (RMDQ) and the Oswestry Disability Index (ODI). We will assess the best method of score linking and create crosswalk tables.Aim 2 will evaluate and refine the Impact Stratification Score (ISS) based on 9 PROMIS-29 items and proposed by the NIH Research Task Force on chronic low back pain. We will evaluate the ISS in terms of other indicators of condition severity and patient prognosis and outcomes and identify cut-points to stratify chronic pain patients into subgroups.Aim 3 will evaluate the strengths and limitations of MTurk as a data collection platform for estimating chronic pain by comparing its data to other data sources.

**Discussion:**

The accomplishment of Aims 1 and 2 will allow direct comparison of results across past and future studies of chronic pain. These comparisons will help us to understand different results from seemingly similar studies, and to determine the relative effectiveness of all pharmaceutical and nonpharmacologic interventions for chronic pain across different trials. Aim 3 findings will provide valuable information to researchers about the pros and cons of using the MTurk platform for research-based data collection.

**Trial registration:**

ClinicalTrials.gov: NCT04426812; June 10, 2020.

## Background

Substantial research has gone into determining the efficacy and effectiveness of pharmaceutical and nonpharmacologic interventions for chronic pain. Pharmaceutical interventions are still most commonly used [1], but a number of nonpharmacologic approaches have now been shown to be efficacious and effective, especially for chronic low back pain (CLBP), and included in guidelines [2–10]. While there is an extensive literature on these interventions for chronic pain, it is challenging to synthesize the findings because of differences in the samples and outcome measures used. The National Institutes of Health (NIH) Pain Consortium’s Research Task Force (RTF) on CLBP noted that these differences make it “difficult to compare epidemiologic data and studies of similar or competing interventions, replicate findings, pool data from multiple studies, resolve conflicting conclusions, develop multidisciplinary consensus, or even achieve consensus within a discipline regarding interpretation of findings” [11],^p1129^. These differences also limit answers to questions such as ‘Which therapies work best? And for whom?’

The lack of common outcome measures and the inability to identify meaningful subgroups of patients prompted the NIH RTF on CLBP to recommend the use of a common minimum data set and a scheme to classify CLBP patients by its impact on their lives [11]. The RTF recommended use of items in the Patient-Reported Outcomes Measurement Information System (PROMIS®)-29 for studies of CLBP but they also agreed that investigators could substitute “legacy” measures (commonly used measures) such as the Roland-Morris Disability Questionnaire (RMDQ [12]) if they preferred. Therefore, studies will likely continue to use a variety of outcome measures.

A number of crosswalks and links between PROMIS and legacy measures have been produced [13, 14] that enable an outcome score on one measure to be translated into a score on another measure. However, crosswalks have not yet been developed for some of the most commonly used measures for CLBP such as the RMDQ and the Oswestry Disability Index (ODI) [15]. In addition to enabling side-by-side comparisons among studies that used different measures, these crosswalks aid in the interpretation of the results of meta-analyses, and enable the harmonization required for detailed individual patient data (IPD) meta-analyses [16, 17]. Aim 1 of this study is to create empirical links between several common measures used in chronic pain studies and the PROMIS-29 to enable comparisons across studies.

The RTF also recommended that subgroups of CLBP patients be identified by stratifying them according to the impact CLBP has had on their lives. The US National Pain Strategy (NPS) has placed a focus on identifying those with high-impact chronic pain [18] and the NPS’s Population Research work group is considering measures of chronic pain impact [19]. Several measures have been used to classify or stratify patients by the impact of their chronic pain [11, 20–23]. The most well-studied of these is the classification scheme based on the 7-item Graded Chronic Pain Scale [21, 24–30]. Those with high-impact versus milder levels of chronic pain on this scale were found to have significantly greater healthcare utilization and higher healthcare costs [19, 21, 25, 31, 32]; worse health-related quality of life [21, 28, 31]; more unemployment and absenteeism [21, 31]; and more opioid use [21, 31, 32]. There is substantial variation across studies in baseline chronic pain impact levels [31]. This variation severely limits comparing the effectiveness of the interventions across studies because any differences could be attributed to variation in patient case-mix at baseline. Pain impact classification enables case-mix adjustment [33] or weighting, and subgroup analyses using methods such as IPD meta-analysis or simulation modeling. Moreover, targeting patients at the same chronic pain impact level would enhance trial efficiency by reducing patient heterogeneity, and researchers could later report on heterogeneity of treatment effect (HTE) using these groupings [34] allowing interventions to be directed at subgroups where they will be the most effective. The RTF’s impact Stratification Score (ISS) is based on 9 of the PROMIS-29 items identified based on analyses of a sample of 218 patients with LBP who received epidural steroid injections [11]. The results showed that the ISS was highly correlated (Spearman correlation) with the RMDQ (0.66) and ODI (0.81) at baseline, and more responsive to changes in symptoms than the RMDQ. The RTF went on to say that “further assessment of the reliability, validity, and clinical utility of this stratification strategy is a high priority.” [11], ^p1137^ But we are aware of only one study to further evaluate this stratification scheme [35]. Aim 2 of this study is to evaluate and refine the ISS to ensure that it creates meaningful impact-based sub-classifications of chronic pain patients.

This study will use data from three sources. Initial analyses will be performed using large existing datasets that contain the PROMIS-29 plus other measures administered to chronic pain patients. Intermediate analyses will be performed using primary data collected from Amazon’s Mechanical Turk (MTurk), and cross-validation will use primary data collected from KnowledgePanel, a nationally representative probability-based sample [36].

MTurk is the most commonly researched crowdsourcing platform in science and it employs over 500,000 participants [37]. Numerous published studies of data collection using the MTurk platform exist in the social science disciplines [38], and there is an emerging literature on its utility for research on clinical populations [39–41]. One of the key reasons MTurk is attractive to researchers is the opportunity for rapid and inexpensive data collection. For example, data collection for small samples can be completed within a few hours, and the payment for research-related tasks is typically set at the federal minimum wage [42]. In addition, MTurk was found to be less costly and yielded higher quality data than samples recruited from Facebook, Google AdWords, or Craigslist [43]. Further evaluation of this efficient data collection method to verify data quality and improve its application could dramatically reduce the cost of future chronic pain research. Aim 3 of this study is to evaluate MTurk as a data collection method in terms of cost, time to complete, data quality, response at follow-up, relationships among variables, and sample representativeness.

In summary, this study consists of two chronic pain measure improvement efforts (crosswalk/links between measures and further development of an impact stratification scheme) and evaluation of an efficient data collection platform (MTurk). These are the specific aims of this study:
Specific Aim 1: Develop and evaluate links or crosswalks between the PROMIS-29 and other common (legacy) measures used for chronic pain so that the results of studies using different measures can be compared.Specific Aim 2: Evaluate and refine the RTF proposed chronic pain impact stratification scheme that is based on 9 PROMIS-29 items.Specific Aim 3: Evaluate MTurk as a cost- and time-efficient method to collect quality data on individuals with chronic pain.

Note that although CLBP is a main focus in this study (i.e., our named measures to link to PROMIS are CLBP measures and it was the NIH RTF on CLBP that developed the ISS), dataset availability and our Advisory Council’s advice may allow us to link PROMIS to measures for other types of chronic pain and to test the ISS in other chronic pain populations [35].

## Methods/design

This study will be performed by researchers at the RAND Corporation and the University of California Los Angeles (UCLA) with input and advice from a seven-member Advisory Council of experts in chronic pain and its measurement and in data collection. The study will use at least three large existing datasets for the initial analyses for Aims 1 and 2. Further analyses will use data collected via MTurk and these results will be cross-validated using data from KnowledgePanel, a nationally-representative probability-based sample. These data collection efforts have not yet begun. Figure 1 shows the overall plan for the study.

**Fig. 1 Fig1:**
[figure not shown]
Overview of Study. Legend: KnowledgePanel = a nationally representative probability-based online survey panel from which we will gather data from a representative sample of chronic pain patients; MTurk = Amazon’s Mechanical Turk, an crowdsourcing platform through which we will gather data from a convenience sample of chronic pain patients; PROMIS-29 = 29-item Patient-Reported Outcomes Measurement Information System; RTF = National Institutes of Health Pain Consortium’s Research Task Force on Chronic Low Back Pain. Aims 1 and 2 use data from three sources for their preliminary, intermediate and final analyses. The first source is made up of available existing data and the last two sources will involve primary data collection. Aim 3 involves additional analyses to establish the usefulness of MTurk as a platform for data collection

The RAND Human Subjects Protection Committee has reviewed and approved this study as exempt (2019–0651-AM02).

### Advisory council

The Advisory Council will meet about twice a year and provide input on priorities, suggest existing datasets we could use and legacy measures for which linking to PROMIS-29 are most important. Members of the Council have also agreed to be available as needed to provide input and answer questions as the study progresses.

### Existing datasets

We have three existing datasets from RAND studies that contain measures of interest and have large enough samples for initial analyses (Table 1). These were collected in the RAND Center of Excellence for the Appropriateness of Care (CERC) study [44–46], Assessment of Chiropractic Treatment for Low Back Pain (ACT) trial [47, 48], and Crowdsourcing for Patient Engagement (MTurk) study [49]. We will use these to begin to create links or crosswalks of the PROMIS-29 scales with the ODI (the CERC and existing MTurk datasets) and the RMDQ (the ACT dataset) and explore crosswalks/links of the PROMIS-29 scales with the Neck Disability Index (the chronic neck pain, or CNP, portion of the CERC dataset). Also, because these datasets include the PROMIS-29, they also include the 9 items that make up the RTF-proposed ISS and can be used for analyses of that measure. These datasets also contain measures of various aspects of individuals’ lives where chronic pain can have an impact—e.g., healthcare utilization, work status, and mood—allowing cut points to be explored.

**Table 1 Tab1:** In-house existing datasets that will be used in initial studies

	CERC	ACT	MTurk	
Sample size	*n* = 2024 (*n* = 518 CLBP only; *n* = 347 CNP only; *n* = 1159 both)	*n* = 750 (*n* = 384 CLBP; *n* = 287 acute LBP; *n* = 79 subacute)	*n* = 5755	*n* = 1444
Population	Chiropractic patients being treated for CLBP and/or CNP	Active military with LBP participating in RCTs on chiropractic	General population	Those with CLBP
Longitudinal?	Yes	Yes	No	No
Average age in years (SD)	48.6 (14.5)	30.9 (8.7)	36.2 (10.9)	37.7 (11.2)
% Female	72.4%	23.3%	52.4%	56.4%
Average pain 0–10 (SD)	3.1 (1.8)	4.6 (2.0)	2.2 (2.3)	3.9 (2.2)
Measures used:				
PROMIS-29	Yes	Yes	Yes	Yes
ODI	Yes	No	No	Yes
RMDQ	No	Yes	No	No
NDI	Yes	No	No	No
Pain NRS 0–10	Yes	Yes	Yes	Yes

*ACT* Assessment of Chiropractic Treatment for Low Back Pain, Military Readiness and Smoking Cessation, *CERC* RAND Center of Excellence for the Study of Appropriateness of Care in CAM: *CLBP* chronic low back pain, *CNP* chronic neck pain, *MTurk* data collected using an Amazon Web Service called Mechanical Turk, *ODI* Oswestry Disability Index, *PROMIS-29* short form of the Patient-Reported Outcomes Measurement Information System, *RMDQ* Roland-Morris Disability Questionnaire, *NRS* = numerical rating scale

In the first year of the study we will use our Advisory Council and other sources to identify other existing datasets which could be mined for this study. Other promising existing datasets include the PROMIS Wave 1 data [50], the American Chronic Pain Association Supplement from 2007 [51], and the PROMIS Profiles-HUI data [52].

### Additional primary data collected via MTurk

Starting in Year 2 of this study the MTurk platform will be used to collect additional data in support of the work involved in Aims 1 and 2. These data will include items or measures not captured (or not captured together) in the existing datasets (e.g., ODI and RMDQ together, the Graded Chronic Pain Scale), and data from targeted subpopulations missing from or not sufficiently represented in the existing datasets (e.g., individuals with more severe CLBP or other types of chronic pain). The specifics of the inclusion and exclusion criteria for the MTurk samples and the items included will be determined through the Year 1 and early Year 2 work using the existing datasets, as well as recommendations from the Advisory Council. Given our past experience recruitment for this survey should take approximately 1 month. In order to assess responsiveness to change for Aim 2, all participants in the initial survey will also be asked to complete a shorter follow-up survey 3 months later.

### Knowledge panel

The KnowledgePanel [36] is a nationally representative online survey panel originally developed by GfK and now owned and maintained by Ipsos Public Affairs. In Year 3 it will be used to cross-validate all study results generated from the other data sources. This panel has more than 55,000 individuals recruited through a probability-based sampling methodology (address-based sampling) that improves population coverage for hard-to-reach individuals and computers and internet access are provided for those who do not have them. Given the large size of the underlying panel, sample sizes for the KnowledgePanel could go as high as 2000 completed surveys of patients with CLBP. The existing panel also allows completed data collection within 2–3 weeks of fielding the survey. In order to assess responsiveness to change for Aim 2, and similar to our plans for the MTurk data, all panelists responding to the initial survey will also be asked to complete a shorter follow-up survey 3 months later.

### Approach to aim 1: links and crosswalks between PROMIS and legacy chronic pain measures

The main effort in this study will be to link elements of the PROMIS-29 to the ODI and the RMDQ, the two most common patient-reported outcomes (PROs) [53] used in studies of CLBP, the most common type of chronic pain [54, 55]. According to one systematic review of CLBP studies, out of 354 randomized trials published between 2001 and 2010, 168 (47%) used the ODI and 132 (37%) used the RMDQ [53]. Thus, the discussion below focuses on the ODI and RMDQ. However, our existing datasets (see Table 1) will also allow us to explore linkages of PROMIS-29 scales to the Neck Disability Index (NDI) [56], the most common PRO used for CNP [57], which is the second most common type of chronic pain [55]. Although below we only discuss our plans for the RMDQ and ODI, our goal will be to use similar methods to also create crosswalks/links between at least two other commonly used PROs and the PROMIS-29.

We will link PROMIS-29 physical function, pain interference and pain intensity scores with the ODI and RMDQ. First, we will assess whether equating, scale alignment, or prediction is appropriate for each pair of measures [58]. We will evaluate whether the PROMIS-29 scales, ODI, and RMDQ measure the same underlying concept (i.e., are “sufficiently” unidimensional to calibrate items on the same metric) using categorical confirmatory factor analytic models for all items in pairs of instruments. For example, we will estimate models that include the 4 PROMIS-29 physical functioning items, the 4 PROMIS-29 pain interference items, the PROMIS-29 pain intensity item, and the 24 RMDQ items. We will estimate one-factor models and evaluate model fit using the comparative fit index (CFI), root mean square error of approximation (RMSEA), and standardized root means square residual (SRMR). CFI values of 0.95 or above, RMSEA values of 0.06 or below, and SRMR values of 0.08 or below will provide support for model fit [59]. We are also mindful of simulation work that shows that fit criteria can be affected by the number of items and the distribution of the data [60, 61]. We will also inspect model modification indices to help determine if modification to the model or a subset of items provide better fit to the data. In addition, we will evaluate the assumption of local independence by examining residual correlations among items; residual correlations of 0.20 or above are indicative of potential violation of local independence [62].

For sets of items in the pairs of instruments that are sufficiently unidimensional, we will fit the item response theory (IRT) graded response model [63] to estimate item parameters (thresholds, discrimination) on the same underlying metric. Given their popularity in a segment of the IRT community, we will also evaluate the relative suitability of the more parsimonious family of Rasch models for graded data (e.g., partial credit model) [64] in parallel to the graded response model by constraining discrimination parameters to be equal (i.e., estimate thresholds only). If we observe sufficiently high correlations among scales (e.g., 0.80) and suitable model fit to items from pairs of scales for either IRT modeling approach, we will use item parameter estimates from fixed-parameter calibration to construct a crosswalk table using expected a posteriori (EAP) summed scoring and crosswalk tables that map raw summed scores from the ODI and RMDQ to the PROMIS-29 physical function, pain interference and pain intensity scores [14, 65]. Although preliminary studies suggest that correlations between entire scales will not be high enough to support this approach for all linking, we will explore the possibility of identifying subsets of items from disparate measures that can be cross-walked in this way.

If the correlations of PROMIS-29 scales and legacy measures are not large enough (0.80 or higher) to support the methods discussed above, we will develop models to predict PROMIS-29 scale scores from the ODI and RMDQ (and vice versa). We will entertain a variety of a models including ordinary least squares regression, the limited dependent variable mixture model, the beta-based regression approach, and Bayesian models. In addition, we will compare estimated scores with observed scores overall and by patient characteristics (e.g., age, gender, duration of low back pain). We will also estimate mean-error and root-mean-squared error for different models. During prediction, we will account for regression to the mean [66]. We will also evaluate whether the prediction equation varies by patient characteristics (age, gender, duration of LBP, etc.) and over time.

We will compare estimated PROMIS scores from the ODI and RMDQ with observed scores within the sample used to derive them and in independent samples (i.e., other existing datasets, new data via MTurk and the KnowledgePanel) [67]. We will evaluate the accuracy of equating and predictions at the group and individual levels. These estimates will be used to provide guidance on the uncertainty in estimates of one measure from other measures in group-level (e.g., research) studies. Based on previous work, we expect that these estimates will also indicate caution in using crosswalks or other links for individuals because of the relatively larger errors. We will provide confidence intervals around estimated scores from one measure to another.

### Approach to aim 2: evaluate and refine an impact subclassification scheme for chronic pain

In 2014 the NIH RTF recommended stratifying CLBP by its impact on patients’ lives according to pain intensity, pain interference with normal activities, and functional status [11]. The RTF’s proposed ISS sums the raw scores from 9 of the PROMIS-29 items covering physical function, pain interference, and pain intensity. The result is a total score with a possible range from 8 (least impact) to 50 (greatest impact) [11]. The NIH RTF allocated approximately equal percentages of individuals into three categories for the ISS: 8–27 (mild), 28–34 (moderate), and 35–50 (severe). We will estimate the percentages in these three ISS categories in each of our datasets. In addition, we will estimate internal consistency reliability and construct validity using Spearman rank-order and product-moment correlations between the ISS and variables with which it is hypothesized to be associated—e.g., healthcare utilization, worker productivity, and mood (depression and anxiety). We will also examine the correlations of the ISS with the ODI and RMDQ.

Further, we will evaluate responsiveness to change in the ACT dataset, MTurk and KnowledgePanel data using ANCOVA with the ISS as the dependent variable and a retrospective rating of change (Compared to 3 months ago, your low back pain is: *much worse, a little worse, about the same*, *a little better*, *moderately better, much better* and *completely gone*) as the independent variable. We will identify which ISS items are most responsive to change and use those reporting “about the same” to estimate test-retest reliability. The components that make up the ISS may differ by individual characteristics such as demographics and length of time patients have had chronic pain. We will examine whether low ISS scores are driven by pain intensity and higher scores by interference and/or physical function (similar to the structure of the Graded Chronic Pain Scale [21]), or if individuals’ scores or ISS categories are being driven mostly by (or by some particular pattern across) pain intensity, pain interference, or physical function. We will compare the grades of chronic pain based on the most well-studied and validated impact stratification scheme, the Graded Chronic Pain Scale [21, 24–30], to the range of ISS to see what this comparison offers in terms of appropriate ISS cut-points.

We will examine the ISS as an independent variable with the retrospective rating of change item as a dependent variable in an area under the curve analysis [68]. The retrospective rating of change item will be coded as improved for people reporting they are moderately better, much better, or pain is completely gone; all other categories will be coded as not improved. Finally, we will examine other dichotomizations of the item to assess the robustness of the estimates.

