### Approach for aim 3: evaluate MTurk as a cost- and time-efficient data collection method

Starting in Year 2, the MTurk platform will be used to collect data in support of the work conducted in Aims 1 and 2. The existing datasets contain the key measures of interest and are large enough to power initial analyses. However, they do not include the broad array of measures that might be useful, and none were intended to be representative of all CLBP patients. For example, the CERC dataset only includes CLBP and CNP patients currently being treated by a chiropractor, and the ACT sample only includes Active Duty military who were chiropractic clinical trial participants. The addition of MTurk data will be used to validate the relationships estimated on the existing datasets to see whether these estimates hold up in other samples, and allow additional measures to be included and tested for relevance before we move to the nationally representative KnowledgePanel sample for final evaluation. The KnowledgePanel data collection will replicate measures and participant characteristics captured in the new MTurk data. Therefore, we can evaluate the utility of the MTurk platform by comparing those data to the nationally representative sample from KnowledgePanel.

The new MTurk data collection will include chronic pain measures not previously concurrently collected in the other existing datasets (e.g., both the ODI and RMDQ) and will capture these measures in broader chronic pain populations. For example, a number of studies now indicate the importance of patient catastrophizing on chronic pain outcomes [69–72], and that the benefits of certain therapies are affected by changes in catastrophizing [73–77]. Catastrophizing is included in the CERC and existing MTurk datasets, however, a more detailed analysis of its effects related to the RMDQ might be desired. Also, the Graded Chronic Pain Scale [21] is not included in our existing datasets and given its extensive use it would be good to compare its grades to the ISS scores seen. Finally, patients’ retrospective rating of change, used in test-retest reliability and the sensitivity of measures to change, is captured in the ACT data, but not in the CERC or existing MTurk data.

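### The item responsiveness ranking, AUC and test-retest group for the three-domain ISS rest on one rating of change in low back pain, which tends to favour the pain-intensity item

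*Protocol article*

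**What the plan says.** The Approach to aim 2 section of the protocol article states that the ISS "sums the raw scores from 9 of the PROMIS-29 items covering physical function, pain interference, and pain intensity". The Approach to aim 1 section gives the split: "the 4 PROMIS-29 physical functioning items, the 4 PROMIS-29 pain interference items, the PROMIS-29 pain intensity item".

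For change over time, Approach to aim 2 says "we will evaluate responsiveness to change in the ACT dataset, MTurk and KnowledgePanel data using ANCOVA with the ISS as the dependent variable". The independent variable is a seven-category item beginning "Compared to 3 months ago, your low back pain is". It continues: "We will identify which ISS items are most responsive to change and use those reporting “about the same” to estimate test-retest reliability". The next paragraph of that section uses the same item, dichotomized, as the outcome in an AUC analysis. The stated robustness check is to try other dichotomizations of it. The Approach for aim 3 section again refers to a single rating for both purposes: "patients’ retrospective rating of change, used in test-retest reliability and the sensitivity of measures to change".

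No rating of change in function, interference or overall impact is named. The Oswestry and Roland-Morris scores enter Aim 2 as correlates of the ISS, and the Graded Chronic Pain Scale enters for cut-points. Neither is used as a criterion of change.

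**The concern.** Ranking items by responsiveness is a fair comparison only if the external criterion is about equally close to all of them. Here the items come from three domains and the criterion is worded for one. The pain-intensity item is closest to it. The interference items are at one remove, though they are themselves about pain. The function items are furthest away.

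A respondent whose back pain is unchanged but whose physical function has moved would properly answer *about the same*. In the ranking, that true change counts against the function items. In the test-retest analysis, it counts as measurement error. Re-cutting the pain rating at another category cannot reveal the problem, because every cut is still a cut of the pain rating.

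Aim 2 is meant to evaluate and refine the ISS. A ranking that partly reflects the anchor could be read as a property of the items.

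**Working it through.** **The plan's own figure.** On the range, the article says: "The result is a total score with a possible range from 8 (least impact) to 50 (greatest impact". Assume the eight function and interference items are scored 1 to 5 and the pain item 0 to 10. The minimum is then 4 + 4 + 0 = 8 and the maximum 20 + 20 + 10 = 50, so the stated range reproduces. Of the 50 − 8 = 42 points, pain intensity supplies 10 (10/42 = 24%). Function and interference supply 16 each, together 32 (32/42 = 76%). The anchor therefore matches directly the domain that carries about a quarter of the score range.

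**Direction of the effect on the ranking.** Let rho be the correlation between true change in pain and true change in function. Let all items detect change in their own domain equally well. If the anchor reflects pain change plus noise, then

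corr(function item change, anchor) = rho × corr(pain item change, anchor).

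The function item is penalised whenever rho < 1 and not at all when rho = 1.

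**Illustrative size.** The documents give no parameters, so all of these are assumptions:
- True change in each domain: mean 0.3, SD 1.
- Item error: SD 0.5.
- Anchor: true pain change plus noise of SD 0.5.
- *About the same*: anchor within ±0.4. Improved: anchor above 1.0.
- Baseline SD: 2.
- Real change: absolute true change above 0.8.

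Under these settings the pain item has a standardized response mean (SRM) of 1.74, an AUC of 0.89 and a retest correlation of about 0.92. About 10% of its stable group has really changed. For a function item with identical true change and error:

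| rho | SRM | AUC | Stable group with real function change | Retest correlation |
|---|---|---|---|---|
| 1.0 | 1.74 | 0.89 | 10% | 0.92 |
| 0.9 | 1.48 | 0.85 | 20% | 0.90 |
| 0.7 | 1.10 | 0.77 | 32% | 0.88 |
| 0.5 | 0.81 | 0.69 | 38% | 0.86 |
| 0.3 | 0.58 | 0.61 | 42% | 0.85 |

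**Variance left in the stable group.** Under joint normality with unit variances,

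Var(function change | stable) = (1 − rho²) + rho² × Var(pain change | stable).

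The first term is a floor: 0.51, 0.75 and 0.91 for rho = 0.7, 0.5 and 0.3. With the settings above, Var(pain change | stable) is about 0.23, so the totals are:
- rho 0.7: 0.51 + 0.49 × 0.23 = 0.62
- rho 0.5: 0.75 + 0.25 × 0.23 = 0.81
- rho 0.3: 0.91 + 0.09 × 0.23 = 0.93

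At rho = 1 the 0.23 still remains, so part of the contamination is noise in the anchor and not domain mismatch.

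These are shares of change variance, not the bias in a reliability coefficient. For the coefficient, baseline variance is 2² = 4 and error variance 0.5² = 0.25, so

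retest r = 4 / √[4.25 × (4.25 + Var(change | stable))].

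With 0.23 this is 0.92. With 0.93 it is 0.85.

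**Total score.** A similar illustration weighted the domains 10/16/16, with a baseline correlation of 0.7 between domains and interference change closer to pain than function change is. The retest correlation of the total moves from about 0.95 to between 0.95 and 0.93 for rho from 0.9 to 0.3. It would move more if true change were large relative to baseline spread.

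**The case against.** The strongest reply is that the size is unknown. It rests on a correlation the documents do not give and on the assumption that all items detect change in their own domain equally well. The item also asks about the respondent's back pain and not about its intensity. Some will answer for the condition as a whole, which would soften the effect. Interference items are themselves about pain, so the mismatch is weaker there. All of this stands. It limits how firmly the effect can be stated, but not its direction whenever the correlation is below 1.

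A second reply is that little depends on the ranking. A reader might infer that function items will be dropped or down-weighted because of the anchor. The article does not support that: it says the most responsive items will be identified, and it states no rule that removes, weights or rescores items. The ISS is also evaluated through its correlations with the disability measures, healthcare utilization and productivity, through examination of which domain drives scores, and against the Graded Chronic Pain Scale. These are not criteria of change, but the evaluation does not rest on the pain rating alone.

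Third, a single common rating makes ACT, MTurk and KnowledgePanel comparable, and the survey content is still open. Both are true. They are reasons to keep the pain rating and add to it.

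**Conclusion.** The point holds as a weakness in a stated design choice. One pain rating is the only named criterion for the ANCOVA, the item ranking, the stable group and the AUC, and its only sensitivity check stays within that rating. To the extent that function change departs from perceived pain change, the ranking is tilted towards the pain-intensity item: clearly for function items, less so for interference items. Under the assumed settings the tilt runs from small (AUC 0.85 against 0.89 at a correlation of 0.9) to large (0.61 against 0.89 at 0.3).

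The test-retest consequence is secondary. A stronger reading would be that test-retest reliability of the total score is seriously understated. Neither the documents nor the illustration show that: the drop is at most about 0.02 under the assumptions used. Nor can the range of 51% to 91% from 1 − rho² be read as a bias in reliability. It is a lower bound on the share of true function-change variance left in the pain-stable group.

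A reader might also infer that ACT holds no other change rating. Approach for aim 3 says only that this rating is captured there.

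**What to change.** - In the MTurk and KnowledgePanel 3-month follow-up surveys, add one parallel retrospective item on change in the ability to do daily activities, with the same kind of response options. Methods/design says these data collections have not begun, and the MTurk section leaves the survey items open.
- Report item responsiveness and AUC against both anchors, with each anchor's correlation with ISS change, so that readers can see how far the ranking depends on the anchor.
- Estimate test-retest reliability in respondents who answer *about the same* on both items, and report the pain-only definition alongside.
- In ACT, keep the pain rating. Unless another change rating is available there, use Roland-Morris change only as a secondary, supporting anchor; Table 1 shows that ACT is longitudinal and includes that measure. State that its content overlaps with the function and interference items, so it may tilt the ranking the other way.

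The cost is one survey item in each of two online follow-ups, one further set of analyses, and a somewhat smaller stable group for test-retest.
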